### Ethics Approval

The study protocol will be submitted to the French and the IARC ethics committees once the chatbot-based decision aid has been completed. No individual consent will be required; all participants will be informed of their rights not to participate or to object to the collection of their data. The design phase of the chatbot-based decision aid was approved by the IARC ethics committee (IEC 21-16).

### Study Organization

The project will be coordinated by 2 committees. The steering committee (the AppDate-You Study Group) includes all scientific leaders and their collaborators of the 3 study teams: at the CRCDC-OC, the University of Western Brittany, and the IARC. This committee meets on a monthly basis to discuss all scientific and organizational aspects of the project and to decide on corrective measures to be taken, if necessary.

The scientific committee is composed of experts (an epidemiologist, a public health specialist, a gynecologist, and a sociologist), who are independent of the trial, and the scientific leaders of the 3 study teams. This committee meets once a year to make recommendations on the progress of the trial.

## Results

To date, the AppDate-You study group is preparing and developing the chatbot-based decision aid (intervention). Once the decision aid has been completed and validated, we will conduct the cRCT as described above. Recruitment of women is expected to begin in January 2023. The results of the study will be the subject of a new academic publication.

## Discussion

The HPVss test was recently introduced into the French organized CCS program for women who do not participate in regular screening. The goal of our intervention is to improve the effectiveness of the HPVss strategy among women living in deprived areas. If the proposed intervention is successful, the findings of this trial will inform policy makers and stakeholders to update local guidelines. The intervention would be easy to integrate into the current screening program and expand to other populations. Information tailored to audiences with low health literacy is also appropriate for people with high health literacy [19]. A chatbot-based decision aid solution can also be used in other screening or health programs.

There is vast interest in how to optimize the send/return ratio of HPVss kits. We expect our intervention tool to be accepted by women, with a large impact on women’s participation in CCS. First, this is a validated framework based on a collaborative decision-making process among women, health professionals, health psychologists, decision-making experts, and the AppDate-You Study Group and a pilot study to ensure the feasibility and acceptability among the targeted women. Second, the COVID-19 pandemic has accelerated the adoption of digital uses; the French government and citizens turned toward digital technologies to respond to the health crisis and address a wide range of pandemic-related issues. According to the 2021 Digital Barometer, 94% of respondents in France use e-banking (+ 1 point from 2020), 93% have adopted e-administration (same as in 2020), 91% use e-commerce (+ 3 points), 87% use social networks (+2 points), and 83% use instant messaging (+ 1 point) [32]. Services using AI are up by 6 points and are used by 70% of French people [32].

However, our study has some limitations, including the fact that we are not able to guarantee that only women in the experimental group will use the chatbot-based decision aid; access to the chatbot will not require individual identification or codes. The chatbot will be accessible to everyone, which may bias the final results of our trial. This issue is common to all technology-based interventions, and it is not controllable. The AppDate-You Study Group decided not to evaluate some IPDAS effectiveness criteria, such as (1) “choice made” and (2) “decision-making process,” because these criteria have been widely assessed in several trial situations, which have shown that a decision aid is effective in increasing knowledge, accurate risk perception, and value-based informed choice, and in reducing decisional conflict [16].

Chatbot communication methods are growing rapidly in the health care field. To date, few studies have evaluated the effect of these methods in health care. This study will help inform policy makers and health care professionals.

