### Data Collection and Study Variables

The study data will be generated from the CRCDC-OC database. The source of the CRCDC-OC database is the French health insurance database (*Système National des Données de Santé*; SNDS). This database contains individualized and deidentified data on all medical expenditures and reimbursements. All medical care received in the public, private, or liberal sector is recorded in the SNDS. No additional personal or clinical information will be collected during this trial. Anonymized data for each individual participant will be received, stored, and handled at International Agency for Research on Cancer (IARC) using Research Electronic Data Capture, a secure, web-based software platform designed to support data capture for research studies [29,30]. All standard precautions will be taken to ensure the privacy and protection of personal and medical information. Only the principal investigators and coinvestigators as well as the data manager will have access to the data.

This database enables access to some data on women’s characteristics (date of birth, place of residence, and type of health insurance), screening (HPV testing), and further investigations (cytology, colposcopy, biopsy, treatment of precancerous lesions, and surgery).

Real-time usage statistics generated by the chatbot platforms will be used to evaluate women’s use of the chatbot. Chat volumes, response time to women’s chat requests, the number of queries resolved, the main topics in women’s requests, navigation flow, and women’s satisfaction will be analyzed.

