### Secondary Study Outcomes

We will examine whether the intervention also improves the proportion of women providing valid vaginal samples and the proportion of women with invalid HPVss tests who repeat HPVss. We will also compare the detection rate of cervical intraepithelial neoplasia grade 2+ in the 2 groups. Median intervals between the date of the reminder letter and the date of the HPVss test report, and between the dates of sending a positive HPV test result and performing liquid-based cytology will be compared between groups, stratified by age group, place of residence, and health insurance type.

An evaluation of cost-effectiveness will also be performed, to first estimate the cost of the intervention and to calculate the incremental cost-effectiveness ratios as the mean difference in total costs between the intervention and control groups with the mean difference in effects, and expressed as both Euros and US dollars per percentage change in screening participation. Deterministic and probabilistic sensitivity analyses will also be conducted by varying key parameters that may affect the outcome and conclusions of the economic evaluation.

Women’s use of the chatbot will also be assessed through usage and engagement statistics generated by chatbot platforms. We will estimate the average number of messages each participating woman exchanged with the chatbot, the average interaction time spent by each participant and a session-wise split of duration, the average number of failed messages that the Chatbot failed to respond, the most frequently asked questions, and the language most often used to seek information, etc.

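### Chatbot use is planned per participating woman, but anonymous open access with platform-only usage data cannot give that figure for trial women or by arm

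*Protocol article*

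**What the plan says.** Secondary Study Outcomes sets the usage outcomes at the level of the individual trial woman: "We will estimate the average number of messages each participating woman exchanged with the chatbot", and also "the average interaction time spent by each participant".

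Data Collection and Study Variables gives the source: "Real-time usage statistics generated by the chatbot platforms will be used to evaluate women’s use of the chatbot". The same section says that the trial gathers no further personal or clinical information, so no survey of exposure is foreseen.

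The Discussion describes access: "access to the chatbot will not require individual identification or codes". It adds that "The chatbot will be accessible to everyone, which may bias the final results of our trial" and concludes: "This issue is common to all technology-based interventions, and it is not controllable".

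Under Study Procedures, the instructions for reaching the chatbot are described only for the information letter to the experimental group.

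**The concern.** A mean per trial woman needs two things: a way to tell which sessions belong to trial women, and a count of those women as denominator. The access rule removes the first, and no other data source restores it. The Discussion discloses that open access may bias the effect estimate. It does not say that open access also undercuts a stated secondary outcome.

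What is at stake is interpretation. If the trial finds little or no difference, the investigators will want to know how many intervention women used the chatbot. With moderate or high pooled totals they could not separate poor uptake among intervention women from use by others, nor say whether a diluted contrast contributed. Attribution that was not captured at entry cannot be recovered in the analysis, so the choice has to be made before the letters go out.

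**Working it through.** **Setting the statements side by side**

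1. The outcome is per participating woman (Secondary Study Outcomes).
2. The only usage source is the platform's own statistics (Data Collection and Study Variables).
3. The platform receives no identification or code, and anyone can enter (Discussion).
4. No section describes an arm-specific or cluster-specific link, or a question to users, that would tie a session to a trial arm.

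From 2 to 4, total recorded use = use by intervention women + use by control women + use by the public. Only the sum is observed. Dividing it by the number of recorded users gives a mean for an unknown mixture. Dividing it by the number of intervention letters gives at most an upper bound on use per letter. Neither is the quantity in 1.

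**How much dilution could matter (illustration only)**

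The documents give no contamination rate, so the rate is assumed. The other inputs come from Sample Size and refer to the composite well-managed outcome used there: control 15%, experimental 25%, mean cluster size m = 250, intracluster correlation 0.029, coefficient of variation (CV) of cluster size 1.2, two-sided 5%, and 16 clusters per arm, so 16 × 250 = 4,000 women per arm.

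Design effects:
- Without the CV term: 1 + (250 − 1) × 0.029 = 8.22.
- With the CV term: 1 + ((1.2² + 1) × 250 − 1) × 0.029 = 1 + 609 × 0.029 = 18.66.

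Both are shown because the article's own count does not settle which was used. The standard pooled formula gives 250 women per arm before clustering. With 8.22 this needs 250 × 8.22 / 250 = 8.22, so 9 clusters, or 10 with one added, which agrees with the stated 10. With 18.66 it needs 19.

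Effective sample size per arm: 4,000 / 8.22 = 487, or 4,000 / 18.66 = 214.

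Suppose the effect acts only through use, and use in control clusters is a fraction r of use in intervention clusters. Contamination then raises the control proportion to 15% + 10r points and leaves the experimental proportion at 25%. The difference is 10 × (1 − r) points.

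Power = Φ( d / √[(p₀(1 − p₀) + p₁(1 − p₁)) / n] − 1.96 ).

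| r (assumed) | Control v experimental | Difference | Power, n = 214 | Power, n = 487 |
|---|---|---|---|---|
| 0 | 15% v 25% | 10 points | 74% | 98% |
| 10% | 16% v 25% | 9 points | 64% | 94% |
| 20% | 17% v 25% | 8 points | 53% | 87% |

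Worked line for r = 10%, n = 214: (0.1344 + 0.1875) / 214.4 = 0.001501, square root 0.0387; 0.09 / 0.0387 = 2.32; 2.32 − 1.96 = 0.36; Φ = 0.64.

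**The case against.** **The bias is already disclosed.** The authors state openly that access is unrestricted and that this may bias the results. Open access without a login is also a sensible choice for women with low health literacy. This stands, and neither the open access nor the disclosure is criticised here. The disclosure does not cover the usage outcome.

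**The article rules out only individual identification or codes.** It says nothing on arm-level links, the chatbot was still in development, and session-level figures such as navigation flow are foreseen. The format of a link could sit in the full protocol. This has some force, and it is why the point is limited to what is described. Even so, an arm-level link would not deliver a figure per woman, so the outcome needs rewording in any case.

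**The outcome could mean a mean per chatbot user.** On that reading an anonymous average might be computed, but it would describe everyone who opened the tool and would still not divide by arm.

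**Usage is descriptive.** Neither primary outcome uses chatbot data. This stands and limits the weight of the point.

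**Stronger readings that the documents do not support.** A reader might infer that the trial's main comparison is invalid. It is not: groups are compared as randomised, and contamination of this kind pulls the difference towards zero. A reader might infer that contamination is large. Only the experimental letter is described as carrying access instructions, allocation is by cluster, and no rate is given, so it may be small. A reader might infer that a null result could never be explained. Low pooled totals would show non-use, because they bound intervention use from above; only moderate or high totals are ambiguous. Finally, a reader might infer that tagged links would measure control-arm contamination. They would not, as set out under the fix.

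**Conclusion.** The point holds in a limited form. The planned averages per woman and the anonymous, open, platform-only measurement are incompatible as stated: the result would describe an unknown mixture of intervention women, control women and outsiders. This follows from the text alone and holds even if contamination is nil.

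The effect on the primary comparison is possible dilution of unknown size. The power figures rest on assumed dilution of 10% or 20%, on the effect acting only through chatbot use, and on the choice of design effect. With 8.22 power stays above the planned 80% even at 20% dilution; with 18.66 it starts below 80% before any dilution. They show a range and are not an estimate for this trial.

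The change should be made before mailing. It concerns a secondary outcome and the reading of the result, not the validity of the randomised comparison.

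**What to change.** 1. Print a cluster-specific link or QR code in the intervention letters, or at least an arm-specific one, that tags the session by entry route with nothing for the woman to type. Keep the chatbot open to all.
2. Report tagged use by cluster, per letter sent and per session. Show untagged sessions separately as a rough indicator of outside use.
3. Reword Secondary Study Outcomes from use per participating woman to these quantities.
4. State in the Discussion that control-arm use remains unidentified.

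Cost: up to 16 tagged links and a merge field in the letter. Because the chatbot is to be offered through several channels and languages, the tag has to be carried through each of them. The ethics submission is planned for after the chatbot is completed, so the change can be included in it.

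Limits: a shared link will be counted under the cluster that received it, and an intervention woman who searches for the chatbot will be untagged. A control woman who finds it will be pooled with the public, or counted as intervention if she was given a link. The change therefore makes intervention-arm uptake estimable, with some misclassification, and leaves control-arm contamination unmeasured.

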## Appendix

Multimedia Appendix 1 Peer review report.

## Abbreviations

CC: cervical cancer
CCS: cervical cancer screening
CRCDC-OC: Regional Cancer Screening Coordinating Centre of Occitanie
cRCT: cluster randomized controlled trial
HPV: human papillomavirus
HPVss: human papillomavirus self-sampling
IARC: International Agency for Research on Cancer
IPDAS: International Patient Decision Aid Standards
IRIS: Ilots Regroupés pour l’Information Statistique
SNDS: Système National des Données de Santé
SPIRIT-PRO: Standard Protocol Items: Recommendations for Interventional Trials–Patient-Reported Outcomes
